## Abstract

**Background:**

Although psychological interventions for stress relief, such as cognitive behavioral therapy (CBT) and mindfulness-based stress reduction (MBSR), have been developed, they have not been widely used in treating depression. The use of mobile devices can increase the possibility of actual use by integrating interventions and reducing the difficulty and cost burden of treatment application. This study aims to determine whether “inMind,” an integrated mobile application for stress reduction, developed for the general population, decreases stress for patients with mild to moderate major depressive disorder during the pharmacological treatment period.

**Methods:**

This study is a single-blind, multicenter, randomized, controlled crossover trial. The App, developed in Republic of Korea, provides integrated interventions for stress reduction for the general population through three modules based on mindfulness-based stress reduction, cognitive behavior therapy, and relaxation sounds that are known to be effective in stress reduction (“meditation,” “cognitive approach,” and “relaxation sounds,” respectively). Participants (*n* = 215) recruited *via* medical practitioner referral will be randomized to an App first group (fAPP) or a wait list crossover group (dAPP). The study will be conducted over 8 weeks; the fAPP group will use the App for the first 4 weeks and the dAPP group for the next 4 weeks. During all study periods, participants will receive their usual pharmacological treatment. The Depression Anxiety Stress Scale-21 is the primary outcome measure. The analysis will employ repeated measurements using a mixed-model approach.

**Discussion:**

The App can potentially be an important addition to depression treatment because of its applicability and the comprehensive nature of the interventions that covers diverse stress-relieving models.

**Clinical trial registration:**

https://clinicaltrials.gov/ct2/show/NCT05312203, identifier 2021GR0585.

## 1. Introduction

Stress is a factor that causes depression as well as is caused by depression (1, 2). Stress is considered an important factor in both directions in depression because it affects suicidal behavior (3), social relationships (4) and depression itself (5). However, the chronic stress response in depression has not received much attention compared to symptoms such as depression and anxiety (6). Since the effect of antidepressant drug treatment requires several weeks of follow-up (7), an effective tool that can alleviate chronic stress in patients with depression during the treatment period is essential.

The transactional theory of stress explains stress as an interaction between a person and their environment (8, 9), suggesting that a person can deal with stress by identifying stress-related appraisals and modifying their cognition and coping (10). Mindfulness-based stress reduction (MBSR) and cognitive behavioral therapy (CBT) are two psychological approaches that could facilitate increased awareness of stress-related (and other) appraisals, re-evaluation or non-judgmental acceptance of these appraisals, and increased awareness of available options for responding appropriately.

The effectiveness of MBSR in depression among adolescents, young adults, and older adults has been suggested in previous studies (5, 11). These approaches pay less attention to thought-content reframing and behavior modification and more on modifying one’s connection between thoughts and behaviors through meditation practice (12). Mindfulness is characterized by non-judgmental awareness and acceptance of here and now experiences (including thoughts, feelings, sensations), and greater awareness of suitable behavioral choices available (13).

Among the variety of accessible psychiatric interventions, CBT has held a dominant position (14). It is one of the most widely utilized interventions and is recognized as a treatment of choice for depression, either alone or in combination with pharmacotherapy (15). The efficacy of CBT in reducing stress has also been shown in a previous meta-review study (16). CBT for stress-management consists of recognizing how thoughts (including appraisals), feelings, behaviors, and physical sensations interact to cause stress, and then utilizing that understanding to find strategies for preventing or modifying stress (17). Based on the CBT approach (18), possible strategies are recognizing and re-evaluating the accuracy of stress-related beliefs (appraisals), discovering stress-inducing behaviors and substituting more helpful behaviors, and identifying techniques to lower physiological arousal associated with stress (19–21). Through this process, the stress-related maintenance cycle of thoughts, feelings, behaviors, and bodily sensations can be disrupted and replaced with a stress-relieving maintenance cycle.

Stress occurs with a stress system response, involving the amygdala, hypothalamus, autonomic nervous system (ANS), and various hormone glands and organs (22). Several studies have found that chronic stress disrupts the balance of the ANS and causes hormonal system imbalance and inflammation represented by increased cortisol secretion, that affects the occurrence and exacerbation of depression (23). Symptomatic interventions that can reduce these bodily responses have been attempted in non-clinical settings. Listening to relaxing sounds has been shown to lower cortisol levels and help recover from stress (24). Moreover, Alvarsson et al. found that exposure to colors and sounds in the natural environment helps people recover quickly from stress (25).

Applying interventions for stress reduction in clinical settings for patients with depression can be challenging. MBSR and CBT for stress reduction are group or individual-based treatments conducted for 1–2 h per week for several weeks, thus, there is a barrier to their wider implementation due to significant time and economic costs (5, 11). In addition, the use of white noise is relatively advantageous in terms of time and economic cost; however, there is no way to provide it systematically. The recent decline in access to healthcare due to the COVID-19 pandemic has made these limitations even more pronounced (26).

Smart Mental Health Interventions (SMHI) are tools that help overcome these limitations. SMHI delivered *via* applications or text messaging have shown promise in addressing these concerns. They lower hurdles to accessing conventional mental health services, such as cost, stigma, and accessibility (27, 28). The digital nature of SMHI makes it possible to include various treatment components in one application, as well as to keep accurate records of users’ activities, that form the basis for providing appropriate interventions for individuals (29). In addition, current techniques enable bio-signals acquisition using mobile devices, that can help an individual take appropriate action by providing an objective measure of their stress (30, 31). While SMHI may vary in terms of strategy, focus, and mode of delivery, they appear to be as effective as conventional in-person treatment interventions (32).

Since several previous SMHI have tried to investigate the effects of transplanting MBCT, ACT, and CBT, provided by clinics, to mobile devices on psychiatric symptoms such as depression and anxiety (19, 32–36), most of them required direct participation of clinicians and patients. Therefore, to reduce the time cost, it would be helpful to develop SMHI with fully contactless intervention from the therapist. Considering the importance of stress management in the treatment process for depression, developing the adjunct role of SMHI that can be used for a short period for stress relief in depression treatment strategies is essential. However, to our knowledge, there has been no attempt to use SMHI for chronic stress management during depression treatment.

Other than psychiatric disorders, there are examples of SMHI use concerning work-related stress. For example, self-guided internet-based stress management intervention for workers, and mobile apps in connection to the COVID-19 pandemic that emphasized coping strategy development and resilience enhancement, demonstrated a moderate-to-large impact size for stress reduction (37, 38). However, in the context of depression’s susceptibility to stress and pathological cognitive structure, it would be beneficial to incorporate a broader range of interventions and an objective assessment of stress. Given the current heterogeneity and room for improvement in solutions related to stress reduction in patients with depression, there is a need for a well-designed intervention that integrates existing interventions, allowing participants to utilize various components freely and decrease costs by reducing direct intervention from therapists and time of use.

For this purpose, the “inMind” App (from hereon, the App), an SMHI tool that combines relaxing sounds, MBSR, and CBT modules, that can be used independently by users and is being used as a digital wellness tool for the general population in Republic of Korea^1^ is employed. The current study [Alleviating Stress by Mobile Application for Depression (ASMA-D)] investigates whether the App may be an effective solution to overcome the challenges mentioned above.

The aim of the ASMA-D study is to evaluate the efficacy of the App in reducing stress in patients with depression during treatment. We also aim to investigate the feasibility and acceptability of the 4-week mobile application intervention in this setting.

The study’s primary hypothesis is that applying this novel mobile application intervention for patients with mild to moderate major depressive disorder (MDD), for 4 weeks with usual care, will result in greater reduction of stress compared to usual care alone.

## 2. Materials and methods

### 2.1. Design

This study is a single blind, multicenter, randomized, controlled crossover trial (Figure 1). All subjects who meet the inclusion and exclusion criteria will be randomly assigned to the App first group (fAPP) or the wait list crossover group (dAPP). Due to the intervention’s nature, this will be a single-blind study in which the results will be assessed blindly but participants will be aware of their group assignment. Participants assigned to fAPP group will use the App initially for 28 consecutive days (T1). During T1, participants assigned to the dAPP group will maintain their usual treatment. After T1, for the next 28 consecutive days (T2), dAPP will use the App and fAPP will maintain the usual treatment, without a wash-out period. We assume that there would be no carry-over effect as the App utilized in this study is not a curative treatment but rather a tool for relieving stress. Therefore, we have decided to use a cross-over design without a wash-out period. Recommendation for Interventional Trials (SPIRIT) flow diagram is presented in Figure 2.

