### 2.8. Assessments and outcomes

Assessments will be obtained through the clinician rating scale and self-rating scales during hospital visits. Table 2 presents the schedule for assessments. Assessments conducted at the hospital visits were acquired at the baseline (V_0_) and every 2 weeks (V_1_, V_2_, V3, and V4) during T1 and T2. The baseline assessments will be collected when participants are enrolled and will include their sociodemographic and clinical characteristics. All instruments have been translated to Korean with reliable psychometric properties. The data collection process implanted in the objective monitoring module of the mobile App will be activated through an ID issued after enrollment and randomization.

**TABLE 2 T2:** Schedule for assessments.

Assessments	Baseline	Visit			
		**V1**	**V2**	**V3**	**V4**
Mini international neuropsychiatric interview	V				
Depression, anxiety, and tress scale	V	V	V	V	V
Perceived stress scale	V		V		V
Posttraumatic embitterment disorder scale	V		V		V
Nine-item patient health questionnaire	V	V	V	V	V
Hamilton depression rating scale	V	V	V	V	V
Intervention engagement					V

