### 2.10. Primary outcome measures

#### 2.10.1. Depression, anxiety, and stress scale (DASS-21)

The DASS-21 is s a self-report measure of anxiety, depression, and stress, developed by Lovibond for use in varied situations (48). Eun-Hyun Lee developed the Korean version of DASS-21 in 2018 (49). This version was evaluated in Korean-speaking samples and demonstrated that the items had been translated and adapted adequately and appropriately. The Korean version of DASS-21 was assessed on 481 Korean adults, and the Cronbach’s α was 0.93.

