#### 2.11.4. Hamilton depression rating scale (HAM-D)

The Hamilton Depression Rating Scale (HAM-D) is an inventory of questions used to detect and assess the severity of the signs and symptoms of depression in individuals who have been diagnosed with clinical depression (57). The 17-item version of the HAM-D is more widely used than the 21-item version, that includes four extra items that assess symptoms related to depression, such as paranoia and obsession, rather than the severity of the depressive symptoms. The HAM-D was translated and validated in Korean with good internal consistency (Cronbach’s α = 0.76) (58).

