### 2.14. Data management and protection

Most data, including the usage data on the App, will be documented during visits by the research assistant at each participating hospital; the original forms will be stored in a closed cabinet. Additionally, all unidentifiable data will be saved in a Dropbox-based central data management system^2^ weekly. Identifying information will be kept only in a local database isolated from the external network with restricted access. Since the central data management system is mirrored, data confidentiality and accessibility are always guaranteed. The permission to access data will be managed by the study coordinator. We will conduct self-inspection on consent forms and case records through weekly research meetings.

If a patient withdraws their participation in part or full, it will be recorded in the records, and no additional data (as determined by the patient) will be added. The patient’s data will not be used in the analysis and, if desired, will be removed from the project database (only data already used in studies and project outcomes will be excluded). After the data collection is complete, all identifying variables will be physically removed from the rest of the data. The analysis will be carried out in a purely pseudonymous way.

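### The blinded-assessment claim cannot hold for the primary outcome, DASS-21, because participants who know their group rate it themselves; at most it can cover the clinician-rated HAM-D

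*Protocol article*

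**What the plan says.** The Abstract (Methods) labels the trial: "This study is a single-blind, multicenter, randomized, controlled crossover trial". Section 2.1 explains the label: "this will be a single-blind study in which the results will be assessed blindly but participants will be aware of their group assignment". It makes no exception for any outcome.

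The Abstract also fixes the primary endpoint: "The Depression Anxiety Stress Scale-21 is the primary outcome measure". Section 2.10.1 describes that instrument as a "self-report measure of anxiety, depression, and stress".

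Section 2.1 sets the comparator. In the second period, "dAPP will use the App and fAPP will maintain the usual treatment, without a wash-out period"; in the first period the roles are reversed. No sham or attention-control app is described.

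On how data are collected, Section 2.8 states: "Assessments will be obtained through the clinician rating scale and self-rating scales during hospital visits". Section 2.14 adds: "Most data, including the usage data on the App, will be documented during visits by the research assistant at each participating hospital".

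**The concern.** Blinded outcome assessment is meant to stop knowledge of treatment from influencing the recorded value. That requires the person who produces the value not to know the treatment. For a questionnaire filled in by the participant, that person is the participant, and the same sentence that claims blind assessment says participants know their group.

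The stake is the interpretation of the primary hypothesis, which is a greater stress reduction with the App plus usual care than with usual care alone. Someone who has just been given a stress-relief app may report less stress because they expect to. Someone in the first period who knows the app comes later may report more. Both would push self-rated stress in the hypothesised direction without any effect of the App. A trial described as single-blind with blind assessment implies protection against this for its results in general, and the primary result has none.

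**Working it through.** The plan gives no figure on this point, so the check sets the sections side by side.

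**1. Who rates each repeated scale in Table 2?**

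| Scale | Role | Time points | Rater, and basis |
|---|---|---|---|
| DASS-21 | primary | 5 | participant; stated in Section 2.10.1 |
| PSS | secondary | 3 | participant; stated in Section 2.11.1 |
| PTED | secondary | 3 | participant; stated in Section 2.11.2 |
| PHQ-9 | secondary | 5 | participant; inferred from Section 2.8 |
| HAM-D | secondary | 5 | clinician; inferred from Section 2.8 |

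The two inferences rest on Section 2.8, which speaks of one clinician scale in the singular and of self-rating scales in the plural. The HAM-D, described in Section 2.11.4 as "The Hamilton Depression Rating Scale (HAM-D) is an inventory of questions used to detect and assess the severity of the signs" and symptoms of depression, is the only repeated scale that fits the singular. That leaves the PHQ-9 among the self-rated ones. The MINI is a baseline diagnostic interview, and intervention engagement comes from App logs, so neither alters the count.

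**2. Count.** Participant-rated: 4 of 5 scales, or 5 + 3 + 3 + 5 = 16 of 16 + 5 = 21 planned scale administrations. Clinician-rated: 1 of 5 scales, 5 of 21 administrations, none of them the primary outcome.

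**3. Could participants be unaware of their period?** No. Section 2.1 says they know their group, and App use against no App use is self-evident.

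**4. Does other text on blinding rescue the claim?** Section 2.6 describes a program that keeps allocation hidden from researchers before assignment. That is allocation concealment. It does not bear on who knows the treatment when outcomes are recorded.

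**5. Is the HAM-D blind protected?** The HAM-D is collected at baseline and V1 to V4. Section 2.7.1 has the researcher give App instructions according to assigned group and help activate the alarm. Section 2.14 has App usage documented at visits by the research assistant. No section shown says who rates the HAM-D or how that person is kept from this information. Against that, no section says that the rater is the research assistant or sees usage data. Section 2.11.5 limits requests for and evaluation of server data to research assistants, and Table 2 places intervention engagement at V4 only. Unblinding of the HAM-D is thus possible but not shown.

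**The case against.** The strongest reply is that nothing is hidden. The sentence in Section 2.1 itself says participants are aware of their assignment and gives the nature of the intervention as the reason, and Section 2.10.1 calls the DASS-21 self-report. A careful reader can put the two together. An app compared with usual care can hardly be blinded, and no relabelling removes the bias. This stands as far as it goes: the fault is not concealment of the open label, and a sham is not being asked for. But the same sentence says that the results, without exception, are assessed blindly, and for the primary outcome that is untrue.

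A second reply is that blind refers to the analysts. The text speaks of assessment. If analysts are meant, the protocol should say so.

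Several stronger readings are tempting, and the documents do not support them:

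- *The HAM-D is in fact unblinded.* A reader might infer this from usage data being recorded at visits. The rater's identity and access are not stated, and a journal article commonly leaves rater procedures to the full protocol.
- *The bias takes up a definable share of the planned effect of 0.28.* The documents give no size for the bias, and the metric of 0.28 is unclear. With power 0.95 and two-sided alpha 0.05, a total of 168, close to the stated 172, follows if 0.28 is a paired standardised difference or Cohen's f. Read as a between-group d, it would need 332 per arm. Any percentage would rest on an assumed numerator and an uncertain denominator.
- *The HAM-D can serve as a bias-protected check on the primary result.* It measures depression, not stress, and a blinded interviewer still relies on what an unblinded patient reports.
- *All control-period participants are waiting for the App.* That describes the dAPP group in the first period only. In the second period the fAPP group has already used it.

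**Conclusion.** The statement is wrong as written. The trial does not have blinded assessment of its primary outcome, nor of three of its four secondary rating scales. The claim can apply to the HAM-D at most. For the DASS-21, PSS and PTED this follows from the protocol's own descriptions. For the PHQ-9 and HAM-D it rests on the split in Section 2.8.

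No sample size, power or analysis figure changes. The effect is on what the trial can conclude: a DASS-21 difference in favour of the App will be compatible with some contribution from expectation, of a size the documents do not allow one to state. The lack of a described safeguard for HAM-D raters is a lesser point, a risk only, and the conclusion about the primary outcome does not depend on it. The correction should be made, because it is nearly free and bears on the primary conclusion.

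**What to change.** 1. In the Abstract (Methods) and Section 2.1, state that the DASS-21, PSS, PTED and PHQ-9 are participant-rated and unblinded. Limit the blinded-assessment claim to the HAM-D, and add analysts if they are also to be blinded.
2. State that the primary result will be interpreted as open to expectation bias. Treat the HAM-D as supportive only.
3. To protect the remaining claim, have the HAM-D rated by existing staff who did not give App instructions, and before any App usage data are reviewed at that visit.

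The cost is a change of wording and some attention to staff roles and task order within visits already planned. No extra visits or staff are needed. The downside is a less favourable blinding claim.

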**FIGURE 5 F5:**
[figure not shown]
Screenshots of the cognitive approach module. The module includes two parts (**A**: “Emoji and Emotion Diary” and **B**: “Re-Think”). Emoji is a tool for expressing varied emotions; the participant can choose what is presented as a sample or create their own Emoji by selecting a color or shape such as eyes and mouth (A-1). The diary is created by checking the emotional intensity related to the previously created Emoji through the slider and entering the title and details (A-2). Participants can see the content of their diary and the emoji of any particular day through the calendar (A-3). In all steps in the “Re-Think” part, participants write answers to the questions displayed on the screen (B-2), and select emotion cards (B-3). The content was presented in Korean, but the examples in this figure are presented in English to aid understanding for international readers.

The “re-think” component aims to help participants practice changing their negative thoughts into positive ones by highlighting the inter-relationships between thoughts, feelings, physical sensations, and behaviors and dealing with biased thinking that induces negative emotions (19–21). The “re-think” component consists of three steps (Figure 5B). First, participants express their concerns that cause them stress, in detail. Second, they compare the expressed emotions and concerns, and then try to see the actual situation rather than the related emotions. Third, participants advise themselves from a third-person perspective based on the contents expressed up to the previous point. Then, participants are guided to think about the change of emotions about their concerns from the starting point through the previous steps and put it in writing.

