### 2.7. Interventions

#### 2.7.1. Administration of the App

Participants will be instructed to use the App autonomously for 4 weeks at home, in addition to their usual treatment, during the period of using the App (T1 for fAPP group, T2 for dAPP group). According to their assigned group, each participant will receive basic instructions from the researcher on how to use the App.

As the purpose of using the App is to obtain an additional stress relief effect in the usual treatment for patients with depression, the schedule for the App will not be strictly controlled; the researchers will provide a 4-week schedule as a guideline to ensure the use of more than the minimal. As a minimum standard for usage, the schedule will guide participants to use the components of each module at least once a day, 6 days a week or more, and the use of additional content is left to the participant’s discretion. However, regarding the meditation module, the participants will be guided to conduct training after completing psychoeducation in consideration of the characteristics of the content. The App has implemented a system that alerts the user twice per day at a time they select if it is not utilized at least once per day. The researcher will help participants who have provided permission to activate the alarm system in the App. However, whether a participant follows these guidelines is not a determining factor in excluding respective participants’ data.

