### 2.12. Sample size and power calculations

To the best of our knowledge, there are no studies on stress-reduction programs for depression patients using a mobile application; hence, we have assumed the sample size based on the effect size of 0.28, being half of the effect size of 0.56 reported in a previous study that applied MBSR in patients with depression (59). For all patients with depression, the change in DASS-21 score from pre- to post-administration of the App would be analyzed using analysis of variance for a 2 × 2 crossover design (60). As we have assumed no carry-over effects, this was not considered in calculating the sample size. Sample size calculations were conducted using the statistical software G * Power 3.1.9.2 (61). The minimum sample was identified as 172 (fAPP = 86, dAPP = 86) based on an estimated between-group effect on post-intervention stress outcomes between the fAPP and dAPP with a power of 0.95 and an alpha of 0.05. Therefore, the current study will enroll 215 participants and allow for up to a 20% loss to follow-up, expecting a minimum effective sample size of 172 individuals.

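### The no-wash-out crossover assumes zero carry-over without support: persisting skills could dilute a two-period estimate by up to half, and a change score taken from V2 would inflate it by half even if the assumption is true

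*Protocol article*

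**What the plan says.** Protocol section 2.1 fixes two consecutive 28-day periods. After T1, "dAPP will use the App and fAPP will maintain the usual treatment, without a wash-out period". The reason given is "We assume that there would be no carry-over effect as the App utilized in this study is not a curative treatment".

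Section 2.12 carries the assumption into the sample size: "As we have assumed no carry-over effects, this was not considered in calculating the sample size". It also states that "the change in DASS-21 score from pre- to post-administration of the App would be analyzed using analysis of variance" for a 2 × 2 crossover. The next sentences of that section, however, base the 172 on a between-group difference in post-intervention stress between fAPP and dAPP. Section 2.13 names a linear mixed model.

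The App is described as follows:

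- **Section 2.3.2:** the cognitive component "aims to help participants practice changing their negative thoughts into positive ones".
- **Section 2.7.1:** for meditation, "the participants will be guided to conduct training after completing psychoeducation".
- **Section 2.3.1:** the two-week course is meant to teach the participant how to train.
- **Section 1:** the CBT approach is said to replace the cycle that maintains stress with one that relieves it.

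The primary hypothesis, in section 1, is that four weeks of the App with usual care "will result in greater reduction of stress compared to usual care alone".

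**The concern.** A treatment need not be curative for its effect to outlast its use. Two of the three stress-relief modules are presented as learning, and the protocol offers no evidence that the benefit ends when fAPP stops at V2. If some of it remains, fAPP is not a clean usual-care control in T2, and pooling T1 with T2 shrinks the App contrast.

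A second problem points the other way. V2 closes T1 and, with no wash-out, is also the only visit at which a T2 starting value can be taken. In fAPP that value is measured on the App. If the effect then fades, the return toward the untreated level appears as worsening under usual care and is credited to the App a second time.

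What is at stake is the size of the primary estimate and the meaning of the stated 95% power.

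**Working it through.** **Inputs from the protocol.** Effect size 0.28 (metric not named), power 0.95, alpha 0.05, 172 evaluable (86 per group), 20% loss, 215 enrolled (section 2.12); DASS-21 at V0 to V4 (Table 2); no wash-out (section 2.1).

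**Assumed, because the protocol gives no figure.** c from 0 to 1; correlation between visits 0.5 for the crossover; V0-V2 correlation 0.5 to 0.7 for the baseline-adjusted comparison; two-sided testing; the same App effect in T1 and T2.

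**The plan's own figure.** 172/0.8 = 215, exact. At 95% power, the total sample needed is:

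| Reading of 0.28 | Total |
|---|---|
| Paired test, standardised within-person effect 0.28 | 168 |
| Two groups, Cohen's f = 0.28 (d = 0.56) | 168 |
| 2 × 2 crossover, d = 0.28, correlation 0.5 | 166 |
| Two independent groups, d = 0.28 | 666 |

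The first three come within about 4% of 172, so the figure is roughly reproduced, but it does not reveal which metric or contrast was meant. The fourth does not reproduce it.

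**Bias.** Scale the App effect to a fall of 1. Any change over time common to both groups cancels. Expected values at (V0, V2, V4) are (0, -1, -c) for fAPP and (0, 0, -1) for dAPP.

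*End-of-period scores.* Take V2 - V4 in each group and halve the group difference. fAPP: -1 + c. dAPP: 1. Half-difference: (-2 + c)/2 = -(1 - c/2).

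*Change from each period's own start.* Take (V2 - V0) - (V4 - V2). fAPP: -1 - (1 - c) = -2 + c. dAPP: 0 - (-1) = 1. Half-difference: (-3 + c)/2 = -(1.5 - c/2).

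*V2 alone.* fAPP minus dAPP is -1 for every c.

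| c | End-of-period scores | Change scores, V2 as T2 start | V2 comparison |
|---|---|---|---|
| 0 | 100% | 150% | 100% |
| 0.5 | 75% | 125% | 100% |
| 1 | 50% | 100% | 100% |

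**Power, end-of-period scores, 172 evaluable, d = 0.28.** With correlation 0.5 the standard error in SD units is √(2(1 - 0.5)/172) = 1/√172, so the noncentrality is 0.28 × √172 × (1 - c/2) = 3.67 × (1 - c/2). For c = 0, 0.5 and 1 this is 3.67, 2.75 and 1.84, giving power 0.955, 0.78 and 0.45. If instead d = 0.56, the noncentrality at c = 1 is 7.34 × 0.5 = 3.67, so power would still be 0.955; the estimate would nevertheless be halved.

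**Power, V2 comparison adjusted for V0, 86 per group.** Noncentrality is d × √(86/2)/√(1 - r²).

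- d = 0.28, r = 0.5: 0.28 × 6.56/0.866 = 2.12, power 0.56.
- d = 0.28, r = 0.7: 0.28 × 6.56/0.714 = 2.57, power 0.73.
- d = 0.56 (f = 0.28), unadjusted: 3.67, power 0.955.

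**The case against.** **The assumption is openly stated, and persistence is not shown.** Both stand. The relaxation-sound module (section 2.3.3) need not leave a lasting effect, nothing in the protocol quantifies c, and c = 1 is an extreme.

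**The analyses are partly inferred.** Section 2.12 does not say outright that V2 is the T2 starting value, and section 2.13 names no contrast. The first is the natural reading of a pre-to-post change in a crossover without wash-out, but it remains a reading. Model terms may be set out in an analysis plan not shown, so their absence is not counted here.

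**A reader might infer that lasting skills can push the estimate 50% either way.** They cannot. Persistence only dilutes end-of-period scores. The upward error belongs to the change-score analysis, is largest when nothing persists and disappears when everything does.

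**A reader might also infer that carry-over cannot be separated from the effect.** Under the means above, V2 gives the effect and the V4 group difference is (1 - c) times it, so c is recoverable if the App works equally well in both periods. That equality is itself an assumption.

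**The V2 comparison costs power.** This stands if 0.28 is d. At correlation 0.5 the crossover loses to it only when 3.67 × (1 - c/2) falls below 2.12, that is, c above about 0.85. The case for V2 rests on freedom from carry-over bias and fit to the hypothesis, not on greater power. It is still a self-reported outcome in participants who know their group.

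**Conclusion.** The concern holds in bounded form. Zero carry-over is asserted on a rationale that sits badly with the protocol's own account of the App. With end-of-period scores the possible consequence is dilution by c/2, at most 50%; c is unknown, so this is a range and not a prediction. With a V2-based change score, the consequence under the plan's own assumption is a 50% overestimate.

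Both errors multiply the true effect, so neither produces a benefit from an App that has none. The documents do not support a claim of spurious efficacy. The bias factors rest on an equal App effect in both periods. The crossover power figures also rest on d = 0.28 and a correlation of 0.5.

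**What to change.** 1. Name as primary the randomised fAPP versus dAPP comparison of DASS-21 at V2, adjusted for V0. It matches the hypothesis in section 1 and the between-group contrast in section 2.12, and needs no carry-over assumption.
2. Do not use V2 as a baseline for T2. Keep the two-period analysis as supportive, on V2 and V4 scores adjusted for V0, with treatment, period and sequence terms, and state that it assumes no carry-over.
3. Do not let a preliminary test for carry-over choose the analysis.
4. State in section 2.12 whether 0.28 is d or f, and restate power for the V2 contrast.

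**Cost.** Patients, visits and treatment stay as planned. Dropping the change score loses nothing in precision: with equal correlation ρ between visits, its person-level contrast 2V2 - V0 - V4 has variance 6σ²(1 - ρ), against 2σ²(1 - ρ) for V2 - V4.

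The real cost is power for the primary contrast. If 0.28 is d, power at 86 per group is about 0.56 to 0.73. Keeping 95% would need 498 to 340 evaluable, or 623 to 425 enrolled (V0-V2 correlation 0.5 to 0.7), against 215 planned. If 0.28 is f, power is at least 0.95 and the planned 215 suffices (168 evaluable, 210 enrolled).
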